### Overview and study design

2.2

This research design for the study is a non-randomized intervention study (quasi-experimental study design). A non-randomized study design was selected due to some feasibility constraints and logistical challenges. This includes challenges with schools meeting the inclusion criteria, such as the requirement for arable land, access to water facilities, and the presence of agricultural and nutrition teachers. Additionally, to align with policy priorities, ensure feasibility and sustained participation, sites will be selected in collaboration with state and local education authorities as well as community leaders, making random assignment impractical.

The study will be carried out in three Southwest Nigeria states which were selected from six states in the region: Ekiti, Osun, and Ogun. There will be two arms of intervention; one group will receive the school-based gardening of IVFs, and the second group will receive both school-based gardening of IVF and WhatsApp nutrition education. This means all participants will participate in the school-based gardening program of IVFs intervention. In addition, 50% (*n* = 130) of the participants will be selected for the nutrition education based on pre-selected criteria such as access to a web-supported phone and knowledge using social media like WhatsApp. Figure 1 summarizes the flow of activities in the study.

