### Participants information and outcome of measures

2.4

Using surveys administered by trained enumerators, information about participants’ socio-demographics and the outcomes of measures includes knowledge of nutrition, dietary habits, food security, anthropometrics and biomarker indicators will be obtained at baseline and post-intervention. Acceptability of the intervention will be included in the post-intervention survey. Information about their engagement, and knowledge retention intervention will be tracked during the WhatsApp nutrition education delivery. Table 2 describes the study activities in details.

The validity and reliability of the tools used to measure study outcomes is described below. All adapted and newly developed tools described below will be assessed for internal consistency by calculating Cronbach’s Alpha to determine the correlation between items measuring each construct.

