### Data analysis

2.5

Descriptive statistics such as frequency and percentages will be used for the socio-demographic characteristics (such as age, gender, student status, and household size) and other outcome of measures (such as knowledge retention, intervention acceptability, and nutrition-related outcomes) that are categorical variables, while mean and standard deviation will be used for the continuous variables. To assess the possibility of bias resulting from missing data, we will conduct sensitivity analyses by carrying out complete case analyses. As opined by Braun and Clarke, this will ensure the robustness and credibility of our result (61). Mixed model analyses will be used to assess the intervention’s impact on skin carotenoid levels, anthropometrics, and diet diversity score (62, 63). The mixed model analysis was chosen because it accounts for repeated measures and can effectively address issues related to missing data. In these analyses, the intervention arms will be treated as the fixed effect so that the measure’s outcome change between the school gardening-only participants and school gardening and nutrition education participants can be assessed by the coefficients or estimated using the least square means. Time and intervention arm will be included as both main effects and interaction effects. The random effect will account for variability variations between groups that might affect the response. We will control for participant’s age, gender, household size, youth status (out-of-school vs. in-school status), community, and state, by including them as covariates in the adjusted models of the mixed model analysis. Mann–Whitney U Test will be used to compare the acceptability of the nutrition intervention between the groups. The analysis will be performed using IBM SPSS (version 23), and the statistical significance will be set at *p*-value <0.05.

As described by Braun and Clarke (61), the participants’ audio (sessions responses) and video recordings (tasks) from WhatsApp engagement will be analyzed using thematic analysis. We will use inductive coding to deduce the theme directly from the data. The convergent mixed method will be used to integrate the qualitative analysis with the quantitative results. This ensures a proper understanding of how participants experienced and engaged with the intervention.

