While the study involves self-reported outcomes and other measures, enumerators will be trained before the data collection period to uphold participant confidentiality to encourage honest responses and reduce response bias. To further minimize response bias in self-reported data, confidentiality assurances will be emphasized during the consent process. Moreover, the proposed analysis, mixed method, will control confounding factors to minimize the differences in participants’ characteristics and account for variability in the data. Additionally, participant dropout is anticipated; however, oversampling will address attrition, and the mixed model analysis will address missing data. The context-specific approach serves to enhance the relevance of an intervention and its applicability in a given study setting the generalizability may be limited for those regions with totally different infrastructures or sociocultural contexts. Nevertheless, the knowledge acquired provides a valuable learning base for designing comparable interventions in other contexts, still through appropriate contextual adaptations. The study is designed to assess the immediate impact of the intervention on nutritional knowledge, dietary habits, and participation in agricultural activities. The longer-term effects of the intervention, particularly about sustainable nutritional changes and health indicators, will be better understood through future longitudinal or follow-up studies. Future studies should put the study findings into perspective and further clarify the effectiveness of the interventions over time.

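### Covariates entered without time interactions leave the arm-by-time effect essentially unadjusted, so the stated control of confounding is not delivered for covariate-related change

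*Protocol article*

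**What the plan says.** Section 2.5 (Data analysis) names a mixed model for skin carotenoid level, anthropometrics and dietary diversity score. The effect of interest is the difference between arms in outcome change: "Time and intervention arm will be included as both main effects and interaction effects". Age, gender, household size and youth status are controlled together with "community, and state, by including them as covariates in the adjusted models of the mixed model analysis". No covariate-by-time term is stated.

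On the variance structure, the same paragraph says "The random effect will account for variability variations between groups that might affect the response", and also "The mixed model analysis was chosen because it accounts for repeated measures and can effectively address issues related to missing data".

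Outcomes "will be obtained at baseline and post-intervention" (section 2.4), which gives two visits. Participants enter the education arm "based on pre-selected criteria such as access to a web-supported phone and knowledge using social media like WhatsApp" (section 2.2). Section 3.1 acknowledges selection bias and then says the analysis "will control confounding factors to minimize the differences in" participants' characteristics.

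**The concern.** The study is not randomised, and covariate adjustment in this model is the stated analytic protection against confounding. The listed covariates are essentially constant over the study. Gender and state do not change, and age advances equally in both arms. The eligibility rules in section 2.2.2 require in-school youths to stay enrolled and out-of-school youths to stay resident for another year, which largely fixes youth status and community.

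A main effect of a constant covariate shifts a participant's level at both visits by the same amount. It says nothing about that participant's change. If older or in-school youths would change differently anyway, and the arms differ on those characteristics because phone access does, the difference is credited to the WhatsApp education. The result would still be reported as adjusted.

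**Working it through.** **Inputs from the protocol article.** Two visits (section 2.4, Table 2); arm, time and arm-by-time as fixed effects, with six covariates (section 2.5); 130 per group and 10% dropout (section 2.2.1), so 130 × 0.9 = 117 per arm; significance level 0.05, taken as two-sided. The sample size reproduces: 1.96² × 0.188 × 0.812 / 0.05² = 234.6, i.e. 235, and 235 / 0.9 = 261, close to the stated 260. It does not bear on this point otherwise.

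**Assumed, because the article gives no values.** Outcome SD 1, pre/post correlation r, size of the imbalance between arms, and the effect of the covariate on change.

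**Step 1, algebra.** Let x be constant over time and u the participant's own level:

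Y(t) = a + b·arm + c·t + d·arm·t + e·x + u + error

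Subtracting the visits gives change = c + d·arm + error difference. Both x and u cancel, so with complete data the estimate of d is the crude difference in mean change, whatever e is. Adding f·x·t gives change = c + d·arm + f·x + error difference, and d is now adjusted for x.

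**Step 2, numerical check.** Data were simulated with 260 participants, one covariate related to arm (log odds 1 per SD), r = 0.6 and no true effect. Over 40 complete data sets, the arm-by-time estimates with and without the covariate main effect differed by at most 8 × 10⁻¹⁵. With 10% random dropout, the main effect moved an estimate by at most about 0.02. Mean bias was 0.334 unadjusted, 0.333 with the main effect and 0.008 with covariate by time.

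For complete data, 2,000 simulations per row under a true null gave:

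| Covariate effect on change (SD per SD) | Bias, crude or main effect | Rejection | Rejection with covariate by time |
|---|---|---|---|
| 0.1 | 0.08 SD | 12% | 5% |
| 0.2 | 0.17 SD | 32% | 6% |
| 0.4 | 0.33 SD | 79% | 5% |

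**Step 3, an illustration in this trial's terms.** Suppose 40% of one arm and 70% of the other are in school, and youth status shifts change by 0.3 to 0.5 SD.

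- Bias = 0.30 × 0.3 = 0.09 SD to 0.30 × 0.5 = 0.15 SD.
- SE of arm by time = √(2 × 2(1 − r)/n) = √(2 × 2 × 0.5/117) = 0.131 at r = 0.5.
- Bias/SE = 0.69 to 1.15, so two-sided rejection under the null is 10.6% to 20.9%.

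**Step 4, the random effect.** If the random effect were on groups only, with independent residuals, the SE would be √(4/117) = 0.185, larger by 1/√(1 − r) = 1.41 at r = 0.5. In the simulation with 260 participants the group-only SE was 0.171, against 0.147, 0.111 and 0.079 for the participant-level SE at r = 0.3, 0.6 and 0.8, i.e. ratios of about 1.2, 1.5 and 2.2. The point estimate was the same either way. Under that inflated SE, the rejection rates in step 3 would be 1.9% to 5.2%. The false-positive figures in step 3 therefore require a correct participant-level SE.

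**The case against.** - **The text does not say that covariates enter only as main effects.** True. But the paragraph names an interaction for arm and time and for nothing else, so main effects are the plain reading. This is not detail merely left to an analysis plan, because the article itself fixes the covariates and the interaction and claims confounding control from them.
- **Some covariates could vary over time.** Table 2 collects socio-demographics at both visits. Household size could plausibly change, but the others are essentially fixed. A reader might infer that the model cannot adjust at all. That is exact only for complete data and constant covariates.
- **Arm by time already protects against confounding.** It does remove stable baseline differences between arms. Only covariate-related differences in change stay uncontrolled.
- **The random effect.** A reader might infer that it sits on groups instead of participants and that the standard errors are therefore wrong. The article does not support this. Groups are not defined, no sentence excludes a participant term, and the paragraph says repeated measures are accounted for, which a participant intercept or a within-subject covariance would satisfy. What stands is an ambiguity.
- **Better adjustment would not rescue the comparison.** Phone access and WhatsApp literacy define the arms and are not among the covariates. Covariate-by-time terms cannot remove confounding through them. Section 3.1 already concedes selection bias and reduced internal validity.

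**Conclusion.** The point holds for the three outcome domains assigned to the mixed model. As written, the adjusted arm-by-time estimate essentially equals the crude difference in changes: exactly so with complete data and constant covariates, and nearly so with dropout. The control of confounding stated in section 3.1 is therefore not delivered for covariate-related differences in change.

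The algebra rests only on two visits and constant covariates. The size does not come from the documents. The bias of 0.09 to 0.15 SD and the 10 to 20% false positives depend on an assumed 30-point imbalance, an assumed 0.3 to 0.5 SD shift in change, r = 0.5 and a correct participant-level standard error. They show what could happen and are not forecasts for this trial. An inflated standard error cannot be claimed alongside those false-positive rates, since it would bring them down to about 2 to 5%. The random effect remains a matter for clarification.

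**What to change.** In section 2.5, name the arm-by-time coefficient as the effect. Add covariate-by-time terms for age, gender, household size, youth status and community. With complete data this is equivalent to regressing change on arm plus these covariates. Drop state: there are six communities, two in each of three states, so community determines it. Report an ANCOVA adjusted for baseline outcome and the same covariates as a sensitivity analysis.

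In section 3.1, limit the statement on confounding to the measured covariates, and say that phone access and WhatsApp literacy define the arms and cannot be fully adjusted for.

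As a clarification, define groups and state that the random effect or within-subject covariance is at participant level.

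The cost is wording and a slightly larger model. The added terms use 1 + 1 + 1 + 1 + 5 = 9 degrees of freedom, about ten, out of roughly 234 participants expected to complete (2 × 117). No change to data collection is needed.

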#### Intervention plan

2.3.1

The school-based gardening component of the intervention, as illustrated in Figure 3, will kick off with a 2-day workshop among the targeted participants. This workshop will cover topics such as an introduction to IVF farming and seed production process, showcasing the best soil management practices, and nutrition and food safety education. The participants will also be introduced to digital tools in agriculture, particularly the use of virtual assistants to facilitate sustainable and efficient farming practices, streamlining workflows and revolutionizing how young farmers access expert-level advice virtually, at their convenience. They will also educate participants on agribusiness models for farming and farming-related commercial activities. After the workshop, the youths will be apportioned equal plots for farming on school farmland. Through the collaboration of the school authorities and communities, the out-of-school youths will also have plots to use on the school farmland. The participants will be provided with viable seeds and other farm equipment, such as drips, knapsacks, soil improvement materials etc. to facilitate their farming activities. This will give them the opportunity to utilize the knowledge of IVF farming learned during the workshop. The agricultural science teachers in the selected schools will supervise the new farmers’ work to support community ownership. Furthermore, participants will be provided with technical support to guide them on good soil health management using the climate-smart approach throughout the farming year. Technical support will be provided through both physical and virtual approaches. At the initial stage of transplanting, the technical support will be provided weekly and then fortnightly till the vegetables are well established. Specifically, support will be provided physically to farmers in rural or semi-urban areas who have limited access to internet facilities and electricity, ensuring compliance. In contrast, urban participants will receive support through both physical and virtual means. Leveraging virtual support technology will help save costs and reduce risks associated with city traffic.

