##### Intervention acceptability

2.4.2.3

The intervention acceptability metric based on the Theoretical Framework of Acceptability (TFA) developed by Sekhon et al. (58) as shown in Figure 4, will be used to determine the acceptability of the nutrition intervention. A questionnaire that captures the seven domains (affective attitude, burden, ethicality, intervention coherence, opportunity costs, perceived effectiveness, and self-efficacy) of acceptability regarding health-related intervention adapted from (59) will be used. The definition of the domains is adapted from Chen et al. (60) is shown in Table 3. Participants’ feedback on the questionnaire on the acceptability of the intervention will be used to determine the acceptability rate of the intervention.

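### Acceptability is compared between arms by an unadjusted Mann–Whitney test, although arms are formed by phone access and the component each arm rates is not stated

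*Protocol article*

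**What the plan says.** Acceptability is a secondary outcome. Section 2.4 places it in the post-intervention survey only. Section 2.4.2.3 describes a seven-domain questionnaire based on the Theoretical Framework of Acceptability that "will be used to determine the acceptability of the nutrition intervention". Section 2.5 then fixes the between-arm analysis: a Mann–Whitney U test "will be used to compare the acceptability of the nutrition intervention between the groups".

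On the arms, section 2.2 states that "one group will receive the school-based gardening of IVFs, and the second group will receive both school-based gardening of IVF and WhatsApp nutrition education", and that "all participants will participate in the school-based gardening program of IVFs intervention". Half the participants (130) enter the education arm on criteria such as access to a web-enabled phone and familiarity with social media. Section 2.2.2 repeats these as eligibility criteria for that arm. Section 3.1 describes the arms as natural groups based on phone access and acknowledges selection bias.

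On adjustment, section 2.5 says: "Mixed model analyses will be used to assess the intervention’s impact on skin carotenoid levels, anthropometrics, and diet diversity score". Age, gender, household size, youth status, community and state are controlled "by including them as covariates in the adjusted models of the mixed model analysis". Acceptability is not among the mixed-model outcomes.

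**The concern.** Two things are unsatisfactory.

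- **No adjustment.** Allocation depends on characteristics that could plausibly affect how a person rates a programme: phone access, digital literacy, and whatever goes with them, such as age, schooling and urban residence. The plan recognises this for carotenoids, anthropometrics and dietary diversity and adjusts those comparisons. For acceptability it names a test that cannot adjust. Because acceptability is measured only once, no baseline value can absorb pre-existing differences.
- **Rated component not named.** The domains (burden, opportunity costs, perceived effectiveness and so on) are defined by reference to an intervention, and the two arms receive different packages. Without knowing what each arm rates, a reader cannot say what a significant difference means.

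Feasibility is part of the study aim, and the abstract's discussion puts acceptability at the centre of the study. A p-value from this test could be read as evidence that the WhatsApp education is, or is not, acceptable. It could instead reflect who was placed in each arm, or a difference in what was rated.

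**Working it through.** **1. What could be rated.** The article uses the idea of a nutrition intervention in more than one sense:

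- The Introduction counts community gardening among nutrition interventions.
- Section 2.1 uses the term for gardening and WhatsApp education combined.
- Section 2.4.2.1, on WhatsApp engagement, uses it for the WhatsApp programme.

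The gardening workshop given to all participants also has nutrition content: section 2.3.1 lists "showcasing the best soil management practices, and nutrition and food safety education" among its topics. This leaves three readings of the acceptability comparison:

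| Object rated | Common to both arms? | What the between-arm test shows |
|---|---|---|
| WhatsApp course | No; gardening-only youth never had it | Nothing interpretable |
| Each arm's own package | No; the packages differ by design | A contrast of two packages |
| Gardening component | Yes | Acceptability of gardening by arm, not of WhatsApp education |

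None of the three lets the between-arm p-value show by itself that the WhatsApp education is acceptable. The second and third are legitimate questions if the article says which one is meant.

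**2. Which comparisons are adjusted.** Mixed-model outcomes are adjusted for six covariates; acceptability for none. Phone access and digital literacy, which define the education arm, are not among the six. Adding only the listed covariates would therefore reduce selection bias but not remove it.

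**3. Number of completers.** The article's sample size reproduces:

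n = 1.96² × 0.188 × 0.812 / 0.05² = 234.57, rounded up to 235.

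Inflating for 10% dropout gives 262 (235/0.9) or 259 (235 × 1.1), both close to the stated 260. No figure in the article is disputed here. With 130 per arm and 10% dropout, completers are 130 × 0.9 = 117 per arm.

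**4. Illustration of the selection effect.** Assume no true difference in acceptability, but a shift of d standard deviations between arms due to selection alone. The article gives no such value, so d is varied. With a two-sided level of 0.05 (sidedness is not stated) and the Mann–Whitney efficiency of 0.955 relative to the t-test under normality:

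P(significant) ≈ P(Z > 1.96 − d × √(117/2) × √0.955) = P(Z > 1.96 − 7.474 d)

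- d = 0.2: P(Z > 0.465) = 0.32
- d = 0.3: P(Z > −0.282) = 0.61
- d = 0.4: P(Z > −1.030) = 0.85

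A simulation of 4,000 trials per setting with 117 per arm agrees. In each range below, the first figure is for a 5-point scale and the second for a continuous score.

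- d = 0: about 5%
- d = 0.1: about 11%
- d = 0.2: 29–32%
- d = 0.3: 57–60%
- d = 0.5: 94–96%

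**The case against.** The strongest objection is to a reading that the wording of section 2.5 invites. A reader might infer that the arms have no common object to rate, so that any between-arm test is meaningless and should be dropped. The documents do not support that. All participants garden, and both the Introduction and section 2.1 count gardening as, or within, a nutrition intervention. The narrow use of the term appears under WhatsApp engagement, not under acceptability. A contrast of packages would also be coherent: it would ask whether adding ten weeks of WhatsApp tasks changes perceived burden or acceptability, which fits the add-on hypothesis in section 2.1. The questionnaire itself is not shown, so its items may name the component.

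Three further objections have weight.

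- The shifts of 0.2 to 0.4 SD are assumed, and the same arithmetic would apply to any unadjusted comparison in a non-randomized study.
- The Mann–Whitney p-value is not the only readout. Section 2.5 also plans descriptive statistics for acceptability and thematic analysis of WhatsApp recordings, and section 2.4.2.3 an acceptability rate.
- The listed covariates do not include the variables that form the arms, so adjusting for them alone is an incomplete remedy.

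What survives is narrower. The test is unadjusted where the plan's mixed-model comparisons are adjusted, and sections 2.4.2.3 and 2.5 do not name the rated component. The acknowledgement of selection bias in section 3.1 does not cure the first, because the adjustment that section relies on is not applied to this outcome.

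**Conclusion.** The point stands in this limited form. Followed as written, section 2.5 gives a between-arm acceptability p-value that is open to confounding by the way the arms are formed. It can be interpreted only if the rated component is known. Unless the items concern gardening, the arms rate different things, and on no reading does the test alone establish whether the WhatsApp education is acceptable.

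The actual bias cannot be sized from the article. The figures of about 32%, 61% and 85% show only how readily a modest selection effect would reach significance. They rest on assumed shifts, 117 completers per arm, two-sided testing and the normal approximation. The outcome is secondary, so the trial's primary comparisons are unaffected. The change is still worth making before the post-intervention survey, because items not labelled by component cannot easily be separated afterwards.

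**What to change.** In sections 2.4.2.3 and 2.5:

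1. State which component each arm rates. Base the between-arm comparison on identical items about the shared gardening component, or say plainly that it contrasts the two packages.
2. Replace the Mann–Whitney test with an ordinal or linear model for arm, using the covariates already listed for the mixed models. Add phone access and digital literacy from eligibility screening where the arms overlap on them. Where they do not overlap, these variables cannot be adjusted for.
3. Report acceptability of the WhatsApp education descriptively, by domain with 95% confidence intervals, in the arm that receives it.
4. State that residual selection bias remains after adjustment.

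The cost is revised analysis wording, component labels on questionnaire items, slightly more analysis work, and a model assumption in place of a rank test. Phone access and digital literacy would need to be recorded at screening for all participants; no other new data are required.

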**Methods and analysis:**

This is a non-randomized, mixed-methods study involving youths between 15 and 35 years who will participate in gardening activities and/or interactive nutrition education via WhatsApp. Participants will be provided technical support on growing IVFs, while nutrition education messaging via WhatsApp will include texts, images, and videos on nutrition and healthy eating behavior. Data at baseline will be collected on the study’s primary outcomes (awareness and interest in IVFs, household food security, nutritional knowledge and practices, fruits and vegetables intake, food safety self-efficacy, dietary diversity, anthropometric, and biomarker indicators). In contrast, data collection during the intervention and at post-intervention will include the study’s secondary outcomes (WhatsApp engagement, knowledge retention, and intervention acceptability). Mixed model regression and the Mann–Whitney U Test will be used to analyze the data collected. All analyses will be performed using IBM SPSS (version 23), and the statistical significance will be set at a *p*-value <0.05.

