Specifically, the study will assess the impact of a school-based gardening program and WhatsApp-based nutrition education interventions on primary outcomes such as youths’ nutrition knowledge, fruit and vegetable-specific self-efficacy, food security, dietary diversity, anthropometric data, and skin carotenoid level. In this study, school-based gardening refers to structured gardening activities conducted within a school setting involving in-school and out-of-school youths residing in the same community as the school. These activities will engage participants in cultivating and harvesting vegetables to enhance agricultural skills, nutrition awareness, and healthy eating habits. This intervention will be guided by the Cognitive Theory of Multimedia Learning (CTML), Social Cognitive Theory (SCT), and Empowerment Theory (ET), all of which are described in details in the method section below. Furthermore, the study will also examine secondary outcomes such as the participants’ engagement, knowledge retention, and acceptability of the intervention.

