**Null Hypothesis:**
*There is no difference in nutrition knowledge, fruit and vegetable self-efficacy, dietary habits, and biochemical data between youth who receive the combination of school-based gardening of IVFs, and WhatsApp nutrition education compared to those who receive only school-based gardening of indigenous fruits and vegetables.*

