**Alternative Hypothesis:**
*There is a significant difference in nutrition knowledge, fruit and vegetable self-efficacy, dietary habits, and biochemical data between youth who receive the combination of school-based gardening of IVFs and WhatsApp nutrition education compared to those who receive only school-based gardening of indigenous fruits and vegetables.*

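### Six to eight outcomes are called primary, the lists conflict with each other and with the planned models, and one unadjusted 0.05 level covers them all

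*Protocol article*

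**What the plan says.** - **Abstract, Methods and analysis.** Eight items are called primary: "awareness and interest in IVFs, household food security, nutritional knowledge and practices, fruits and vegetables intake, food safety self-efficacy, dietary diversity, anthropometric, and biomarker indicators". Fruit and vegetable self-efficacy is not among them.
- **Introduction, last paragraph.** Six items are given as examples of primary outcomes: "nutrition knowledge, fruit and vegetable-specific self-efficacy, food security, dietary diversity, anthropometric data, and skin carotenoid level".
- **Section 2.1, hypotheses.** Null and alternative cover four domains jointly. The null reads "There is no difference in nutrition knowledge, fruit and vegetable self-efficacy, dietary habits, and biochemical data between youth" in the two arms. The list is not labelled primary.
- **Section 2.4.1, Primary outcomes.** There are seven headings, or eight outcomes if anthropometry and the biomarker are separated. Self-efficacy for indigenous vegetables and fruits (IVF) has its own heading (2.4.1.4). Intake has none; it appears only as what the Veggie Meter is meant to reflect (2.4.1.7). Table 2 follows the same pattern.
- **Section 2.5, Data analysis.** A mixed model is named for skin carotenoid level, anthropometrics and dietary diversity. A Mann–Whitney test is named for acceptability, a secondary outcome. Section 2.4.1.5 gives food safety self-efficacy descriptive statistics.
- **Significance level.** One level is stated twice. The abstract has "All analyses will be performed using IBM SPSS (version 23), and the statistical significance will be set at a" p-value below 0.05, and section 2.5 repeats it ("and the statistical significance will be set at" the same value).

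**The concern.** A reader cannot tell from the article which outcomes carry the effectiveness claim. The outcomes hypothesised, those called primary and those modelled form three different sets. No outcome is given precedence, and the joint hypothesis does not say how many domains must differ before the null is rejected. A favourable result on any one of them, at 0.05, could therefore be presented as success on a primary outcome.

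This matters because section 3.2 already looks ahead to demonstrated effectiveness as a model for school curricula and policy. A claim of that reach needs an outcome set fixed before the data are seen.

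**Working it through.** **1. The lists side by side**

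| Outcome | Abstract | Introduction | Hypotheses (2.1) | Section 2.4.1 | Between-arm model in 2.5 |
|---|---|---|---|---|---|
| Awareness and interest | yes | no | no | yes | none named |
| Household food security | yes | yes | no | yes | none named |
| Nutrition knowledge | yes | yes | yes | yes | none named |
| Fruit and vegetable intake | yes | no | unclear | only via Veggie Meter | none named |
| Fruit/vegetable (IVF) self-efficacy | no | yes | yes | yes | none named |
| Food safety self-efficacy | yes | no | no | yes | none named (descriptive) |
| Dietary diversity | yes | yes | unclear | yes | mixed model |
| Anthropometry | yes | yes | no | yes | mixed model |
| Biomarker / skin carotenoid | yes | yes | as biochemical data | yes | mixed model |

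The unclear entries arise because the hypotheses refer to "dietary habits, and biochemical data", and dietary habits are not a defined outcome in 2.4.1. Two of the four hypothesised domains, nutrition knowledge and self-efficacy, have no named between-arm test.

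**2. Chance of at least one false positive**

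The article states no family-wise error, so there is no figure to reproduce. Inputs: a level of 0.05 per test (abstract and 2.5); two-sided tests, an assumption because the alternative has no direction; one test per outcome, with anthropometrics counted once; success declared if any one is significant.

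For k independent outcomes the chance is 1 − 0.95^k:

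- k = 3 (modelled outcomes): 1 − 0.8574 = 14.3%
- k = 4 (hypothesised domains): 1 − 0.8145 = 18.5%
- k = 6 (introduction): 1 − 0.7351 = 26.5%
- k = 7 (headings in 2.4.1): 1 − 0.6983 = 30.2%
- k = 8 (abstract): 1 − 0.6634 = 33.7%

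Correlated outcomes lower these figures. The article gives no correlations, so a range was simulated with equally correlated normal test statistics (400,000 draws):

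| Assumed correlation | 3 outcomes | 8 outcomes |
|---|---|---|
| 0.2 | 14.0% | 31.9% |
| 0.3 | 13.7% | 29.9% |
| 0.5 | 12.5% | 25.0% |
| 0.7 | 10.9% | 19.1% |

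Only a false result in favour of the combined arm is a false effectiveness claim. That is 0.025 per test: 1 − 0.975^3 = 7.3% and 1 − 0.975^8 = 18.3%, if independent.

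**3. Cost of correcting for it**

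The planned size reproduces: 1.96² × 0.188 × 0.812 / 0.05² = 234.6, rounded up to 235, then about 260 (130 per group) after allowing for dropout. That calculation concerns the precision of one proportion (youth unemployment), so it does not reveal which outcome is primary. With 10% dropout, 130 × 0.9 = 117 per arm remain.

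Detectable standardized difference at 80% power (assumed) = (z for the two-sided level + 0.842) × √(2/117), where √(2/117) = 0.1307:

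- Level 0.05: (1.960 + 0.842) × 0.1307 = 0.37 SD
- Level 0.05/3 = 0.0167: 0.42 SD
- Level 0.05/8 = 0.00625: (2.734 + 0.842) × 0.1307 = 0.47 SD

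These figures ignore clustering by school or community and covariate adjustment.

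**The case against.** Several points on the other side have force.

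- **The number of tests.** A reader might infer that all eight primary outcomes are each tested at 0.05. The article does not say so. It names a between-arm model for three and descriptive statistics for food safety self-efficacy. Its general sentence on significance permits tests of the others but does not specify them. So 14% is the figure best supported by the text, and 34% is an upper bound.
- **How likely a false claim is.** A reader might also conclude that a false claim of effectiveness is likely. The calculation does not support that: even with eight independent outcomes the chance is about one in three in either direction, and 18% in the favourable direction.
- **How far the lists truly contradict.** The introduction offers its list as examples, so being shorter is not in itself a contradiction. The hypotheses are not labelled primary. The Veggie Meter partly reconciles intake with the biomarker. What remains firm is that self-efficacy is primary in the introduction and in 2.4.1 but missing from the abstract, and that the abstract lists intake separately from the biomarker.
- **A conjunctive reading.** The alternative hypothesis joins its four domains. If all four had to be significant, the error would not be inflated. The article does not say that this is the rule.
- **A separate analysis plan.** A multiplicity rule may sit in an analysis plan that is not shown, so its absence alone is no finding. But such a plan needs a defined family of primary outcomes, and this article supplies several that conflict.

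**Conclusion.** The point holds as a conflict in the stated primary outcomes, combined with a single unadjusted 0.05 level and a mismatch with the planned models. If any one significant result is taken as success, the false-positive chance is about 14% for the three modelled outcomes, nearly three times the nominal 5%. It is at most about 34% for eight independent outcomes, or about 25–32% at assumed correlations of 0.5–0.2. Restricted to false results favouring the combined arm, it is about 7% and 18%.

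These figures rest on two-sided tests, one test per outcome and the any-one-suffices reading; none of the three is stated in the article. They describe chance alone. Arms are formed by phone access and social media literacy, so controlling multiplicity would not by itself make the error of the effectiveness claim 5%.

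**What to change.** Use one primary list in the abstract, introduction, hypotheses, section 2.4.1 and section 2.5. Define dietary habits or remove the term, say whether intake is an outcome separate from the Veggie Meter reading, and tie each primary outcome to a named between-arm analysis. Then choose one of two routes:

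1. Name one confirmatory primary outcome at 0.05 and make the rest secondary. Which one is the sponsor's choice. Skin carotenoid level is a candidate: it is measured by instrument and already has a planned model. It runs through all four lists only if the biomarker indicators of the abstract and the biochemical data of the hypotheses both mean the Veggie Meter reading. That is a fair inference, since no other biomarker is described.
2. Keep several primary outcomes, apply Holm across them, and claim effectiveness only for those that pass.

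Either route changes wording only. The first costs no power on the chosen outcome, but the others cannot then support a confirmatory claim. The second raises the detectable difference at the first Holm step from about 0.37 to 0.42 SD with three outcomes, or to 0.47 SD with eight, under the assumptions above. Neither removes bias from non-random allocation.
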